#### Interim analyses {21b}

There will be no interim analysis. The study will continue until the 300 participants have completed the study since there were no anticipated problems that are detrimental to the participant.

### Methods for additional analyses (e.g., subgroup analyses) {20b}

The full analysis set (FAS), the per protocol set (PPS), and the safety set (SS) will be included for analysis. The FAS will be obtained on the basis of intention-to-treat (ITT) population, after exclusion from all randomized subjects who receive at least a single-dose treatment through a minimum and rational method. Last-observation-carried-forward will be applied for the estimation of missing data. The PPS is defined as a set including all patients meeting the eligibility criteria; finishing the treatment without major protocol deviations, with good compliance (between 80 and 120%); and completing the CRF as anticipated. The safety set will include those who receive at least a single-dose treatment with data of safety evaluation. Carry-forward of missing data will not be in demand.

### Methods in analysis to handle protocol non-adherence and any statistical methods to handle missing data {20c}

The full analysis set will be obtained on the basis of intention-to-treat (ITT) population, after exclusion from all randomized subjects who receive at least a single-dose treatment through a minimum and rational method. Last-observation-carried-forward will be applied for the estimation of missing data.

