##### Participant request

Patients will be allowed requesting to quit due to their priority, and then, their treatment will abort, regarded as shedding cases and recorded as “treatment failure.” Reasons for withdrawal will be followed and recorded in symptom diary while CRF of every patients will be saved for data analysis,

When subjects with relief of symptoms are unwilling to continue taking the treatment, they need to stop the medication with the researchers’ consent. And the 4-week follow-up will still be conducted after medication as planned.

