### Sample size {14}

Sample size calculation was performed by using PASS 13. The 4-week treatment effective rate would be adopted as the main evaluation indicator. According to the systematic review published by Zhang et al. [23], when overall symptom relief is regarded as the main evaluation indicator, the effective rate of probiotics was 50% while placebo was 30% in IBS-intervened RCTs. On this basis and combined with clinical experience, it was assumed that the 4-week treatment effective rate of the experimental group was 50% and that of the placebo group was 30%. In the case of *α* = 0.05 and the power of test was 90% (*β* = 0.10), the required sample size would be at least 124 pairs. Considering the certain shedding and withdrawal samples (52 patients), the planned sample size would be 150 cases/group, and the total would be 300 cases (into a 1:1 ratio).

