### Procedure for unblinding if needed {17b}

The blinding will be maintained until serious adverse event occurs. Once blinding is broken, the trial will be aborted and the subject will be marked as a shedding case. The management result will be reported to the supervisor with specific reason, date, and sign recorded on CRF.

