## Statistical methods

### Statistical methods for primary and secondary outcomes {20a}

#### General analysis

Statistical analysis will be performed by using the SAS 9.4 (or updated version) software (SAS Institute Inc., Cary, NC, USA). In terms of data description, quantitative data will be presented as mean ± standard deviation, median, minimum, maximum, lower quartile (Q1), and upper quartile (Q3), respectively. The categorical data will be presented as frequency and percentage. The comparison of the two groups will be analyzed in proper methods according to the type of indicators. The quantitative data from the two groups will be compared on the basis of data distribution (variance homogeneity, normal distribution) using group *t* test or Wilcoxon’s rank-sum test. A chi-square test or Fisher’s exact test (if the chi-square test is not applicable) will be applied on the categorical data, and Wilcoxon’s rank-sum test or CMH-*χ*^2^ test for the ranked data. Two-sided tests will be applied in all statistical tests, and a *P* value equal to or less than 0.05 will be considered statistically significant (except for special instructions).

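### Two conflicting rules score withdrawn patients on the primary responder endpoint (treatment failure or LOCF), neither takes precedence, and the FAS sentence does not say who is removed

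*Protocol article*

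**What the plan says.** All references are to the protocol article.

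- **Withdrawal at the patient's wish** (Criteria for discontinuing {11b}, Participant request): "their treatment will abort, regarded as shedding cases and recorded as" treatment failure. A separate paragraph covers patients who stop because their symptoms are relieved. They stop with the researchers' consent, and "And the 4-week follow-up will still be conducted after medication as planned". It gives them no score on the primary endpoint.
- **Missing data** ({20c}, repeated in {20b}): "Last-observation-carried-forward will be applied for the estimation of missing data". There is no exception for withdrawals. What is carried forward (daily score, weekly status or final responder status) is not stated.
- **Unblinding** ({17b}, repeated in {22}): "Once blinding is broken, the trial will be aborted and the subject will be marked as a shedding case". No outcome value is attached.
- **FAS** ({20b} and {20c}): built on the ITT population "after exclusion from all randomized subjects who receive at least a single-dose treatment through a minimum and rational method".
- **Primary endpoint** (Outcomes {12}): a responder must meet both the pain and the stool criterion, each in at least 2 of the 4 treatment weeks.
- **Sample size** ({14}): "it was assumed that the 4-week treatment effective rate of the experimental group was 50% and that of the placebo group was 30" per cent, 90% power, 124 per group, raised to 150 per group by an allowance of 52 patients.

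**The concern.** The failure rule and the LOCF rule cover the same patients on the same endpoint and can give opposite answers. Take a patient who meets both weekly criteria in weeks 1 and 2 and then asks to leave. Under Participant request this patient is a failure. On the observed or carried-forward diary the patient is a responder. If weekly status is what is carried forward, a single good week before leaving is enough.

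If the conflict stays open, the primary scoring rule could be settled after dropout patterns, or even results, are known. The rules also differ in substance. Failure scoring counts withdrawal itself as a bad outcome, while LOCF assumes that a patient who left while well stayed well. The analysis population has a similar weakness, because the FAS sentence allows removals without naming them.

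**Working it through.** **1. The plan's own figure.** Inputs from {14} and General analysis: p1 = 0.50, p2 = 0.30, power 90%, alpha 0.05 ("equal to or less than 0.05 will be considered statistically significant"), two-sided ("Two-sided tests will be applied in all statistical tests"). Pooled-variance formula, no continuity correction:

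n = [1.960·√(2·0.40·0.60) + 1.282·√(0.50·0.50 + 0.30·0.70)]² / 0.20² = 124 per group.

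This matches. The allowance also matches: 300 − 2·124 = 52; 52/300 = 17.3%; 124/(1 − 0.1733) = 150. The sample size is therefore correct for an analysis that leaves dropouts out (124 per arm, power 90.0%). That is neither of the two stated scoring rules.

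**2. Effect on one arm's response rate.** Assumptions, none from the article: one combined weekly response status with probability 0.3 to 0.5, within-patient correlation 0.5, last observed week uniform on 1 to 3, weekly status carried forward. In simulation (400,000 patients per setting), LOCF scores about 32% of dropouts as responders at a weekly rate of 0.3 and about 53% at 0.5.

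- 0.173 × 0.32 = 5.5 points of the arm's rate
- 0.173 × 0.53 = about 9 points
- Under failure scoring, dropouts contribute 0.

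Varying the correlation from 0.3 to 0.7 gives 31% to 54%.

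**3. Effect on the comparison.** 150 randomised per arm and 26 dropouts per arm. The 50% and 30% are read as rates among completers, because {14} adds dropouts on top of 124. Let p̄ be the mean of the two rates. Then:

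Power = Φ{[(p1 − p2)√n − 1.960·√(2p̄(1 − p̄))] / √(p1(1 − p1) + p2(1 − p2))}.

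- *Failure scoring:* p1 = 0.50·124/150 = 41.3%; p2 = 0.30·124/150 = 24.8%; difference 16.5 points. Power = Φ[(0.1653·12.247 − 1.960·0.6653)/0.6550] = Φ(1.10) = 86.4%. For 90%, 169 per arm would be needed.
- *LOCF, dropouts respond at completers' rates (assumption):* 50% vs 30%. Power = Φ[(0.20·12.247 − 1.960·0.6928)/0.6782] = Φ(1.61) = 94.6%.
- *LOCF, dropouts at half those rates (assumption):* 45.7% vs 27.4%, power 91.1%.
- *LOCF, dropouts at 30% in both arms (assumption):* 46.5% vs 30.0%, power 84.1%.

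**4. Unequal dropout under failure scoring** (assumption, same total of 52).

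- 36 experimental, 16 placebo: 0.50·114/150 − 0.30·134/150 = 38.0% − 26.8% = 11.2 points.
- 16 experimental, 36 placebo: 0.50·134/150 − 0.30·114/150 = 44.7% − 22.8% = 21.9 points.

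**5. Scoring only the later weeks as non-response is a different rule.** In the same simulation it still makes about 14% to 28% of dropouts responders on their observed weeks. Participant request fails the patient as a whole, which makes none of them a responder.

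**The case against.** The strongest defence is that a recorded failure is not missing, so LOCF never reaches these patients. That reading is possible, but the article does not state it, and the LOCF sentence carries no exception. A separate statistical plan is mentioned under Confidentiality {27} and may settle details. It would still have to overrule one of two sentences that the article already states.

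Several stronger readings are tempting, and the documents do not support them:

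- *The shedding label is a third scoring rule.* It is not. Participant request uses it in the same sentence as treatment failure, and {17b} and {22} use it as a disposition label.
- *The FAS removes everyone who was dosed.* The sentence speaks of exclusion from the randomised, dosed subjects by a minimal method. This most naturally means a few removals from that set. The fault is that it does not say who they are.
- *About 17% of patients have no single outcome.* 52/300 is a planning allowance. The failure rule is written only for withdrawal at the patient's request, and a dropout who is a non-responder under both rules has one outcome. The share is an upper bound.
- *Patients who stop because of relief are failures.* They have their own paragraph, which does not say so.
- *LOCF inflates response or favours the product.* In the simulation LOCF gives 31% to 53% response among dropouts, against 34% to 60% had all four weeks been observed. Power under LOCF can fall on either side of failure scoring.

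It is also fair that a shift in one arm's rate should not be set against the 20-point difference between arms. With equal dropout that difference moves only from 20 to 16.5 points.

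**Conclusion.** The concern holds as a stated contradiction: two rules, the same patients, the primary endpoint and no precedence. At the planned dropout level, as an upper bound, the choice is worth about 5.5 to 9 points of an arm's response rate, given the simulation assumptions and carry-forward of weekly status. With equal dropout, power is 86.4% under failure scoring and about 84% to 95% under LOCF, depending on how dropouts are assumed to respond. Larger movements in the difference need clearly unequal dropout, which the documents neither predict nor exclude.

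The FAS sentence needs rewriting because its exclusions are unspecified. The sample size of 124 and 150 per group is arithmetically right.

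Separately, the 4-week follow-up under Participant request contradicts the 2-week follow-up in the abstract, Trial design {8} and Participant timeline {13}. It falls after the 4-week primary period and adds no weight to the scoring problem.

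**What to change.** - For the primary endpoint, score withdrawn patients as non-responders overall, as Participant request already states, and not by LOCF.
- Apply the same scoring to unblinded and investigator-withdrawn subjects, and state explicitly how patients who stop because of relief are scored.
- Keep LOCF, or another imputation, as a sensitivity analysis only, and name the unit carried forward.
- Rewrite the FAS in {20b} and {20c} as all randomised subjects with at least one dose, analysed as randomised, with any permitted exclusions named.
- Reconcile the 2-week and 4-week follow-up statements.

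The cost is wording plus one sensitivity analysis. The statistical price is lower reported response rates in both arms, and power of about 86% instead of 90% if dropout reaches the planned level. The sponsor should accept that knowingly or revisit the sample size.

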#### Intervention description {11a}

Subjects of two groups will receive three tablets of either the *Bifidobacterium* quadruple viable tablet or the matched placebo three times a day at 30 min after breakfast, lunch, and dinner, respectively, for consecutive 4 weeks. During the treatment period, researchers will give subjects physical exams and record the results as well as vital signs. Subjects are supposed to keep completing the symptom log every day and record remedial medication and any other drug history permitted in this trial. HAMA, HAMD, IBS-QOL, and laboratory tests will be updated at the end of treatment period.

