##### Quality of life

Subjects will be asked to finish IBS-QOL scale at baseline (week 0), the end of treatment period (week 4), and follow-up period (week 6) successively.

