##### Changes of microbiota and metabonomics

Stool samples of subjects will be collected at baseline (week 0) and the end of treatment period (week 4) to study whether changes of microbiota and metabonomics occur after the treatment.

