## Data collection and management

### Plans for assessment and collection of outcomes {18a}

A training regarding the trial-related procedure will be conducted by the principal investigator for all staff members participating before the implementation of the trial.

In the screening period, data of following contents will be collected:
General information including demographic characteristics (gender, age) and previous and present medical history.Scores of Hamilton Anxiety and Depression Rating Scales (HAMA and HAMD) investigated by the trained raters.Physical examination (general and abdominal) and vital signs including temperature, heart rate, respiratory rate, and blood pressure.Laboratory tests including blood routine, urine routine, stool routine, and occult blood test; fasting blood glucose; tests of liver and kidney function; and electrocardiogram.Abdominal ultrasonography and colorectal colonoscopy. Urine pregnancy test only in women of childbearing age.Complete the symptom log everyday including the strength of abdominal pain, fecal traits, level of overall symptom relief, patterns of defecation, remedial medication, and any other drug history permitted in this trial.Adverse events and concomitant medication.

Patients who are admitted in the trial will be allocated randomly into two groups in a ratio of 1:1, heading to the double-blind treatment period.

In the baseline period, investigator shall give subjects physical exam again and subjects will be required to complete the IBS-QOL (quality of life) scale. Data will be recorded in CRF. Feces will be collected to study the microbiome and metabolome at this period.

In the follow-up period, subjects shall update HAMA, HAMD, and IBS-QOL again, and insist to complete the symptom log and records of concomitant drugs and adverse events every day. Researchers shall perform physical exam and record the results and vital signs as same as previous times.

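### LOCF is fixed for the full analysis set without restriction, but IBS-QOL is scheduled only at weeks 0, 4 and 6, so a missing score is normally filled with one from a different treatment phase

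*Protocol article*

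**What the plan says.** Protocol article, section {20c}, sets the rule straight after defining the FAS: "Last-observation-carried-forward will be applied for the estimation of missing data". Section {20b} repeats it with the analysis sets. Neither place names an outcome, a second method or a sensitivity analysis. The only exemption, "Carry-forward of missing data will not be in demand", follows the safety set definition and reads as covering that set alone.

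The Quality of life section gives the schedule: "Subjects will be asked to finish IBS-QOL scale at baseline (week 0), the end of treatment period (week 4), and follow-up period (week 6"). Other sections agree with it. In the baseline period "subjects will be required to complete the IBS-QOL (quality of life) scale" (section {18a}). The only on-treatment assessment comes at the end: "HAMA, HAMD, IBS-QOL, and laboratory tests will be updated at the end of treatment period" (section {11a}). Section {13} puts treatment at days 1 to 28 and follow-up at days 29 to 42, so week 4 ends treatment and week 6 is off treatment.

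Two further statements bear on patients who leave. The withdrawal criteria in {11b} record those who ask to quit as treatment failures. Section {18b} says that the latest outcomes are recorded at withdrawal, without naming instruments.

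**The concern.** Carrying forward is least harmful when the last value lies close in time to the missing one and under the same treatment. The IBS-QOL schedule meets neither condition. It has one value before treatment, one at its end and one two weeks after it.

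Filling week 4 from week 0 enters a change of zero for that patient. Filling week 6 from week 4 reports an on-treatment score as an off-treatment one. The filled values are then tested as though they had been observed.

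Three consequences follow. The treatment difference shrinks when losses are equal. A spurious difference can appear when both arms improve and losses are unequal. Persistence at week 6 is overstated if benefit fades after stopping; the documents give no figure for fading, so that part stays conditional.

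**Working it through.** **Planned loss.** Section {14} assumes 50% versus 30% response, α = 0.05 and 90% power; section {20a} makes tests two-sided. The pooled-variance formula without continuity correction gives 124 per group, as stated. Then 300 − 2 × 124 = 52 and 52/300 = 17.3%, which reproduces the allowance. It was sized for the primary endpoint and is not a forecast of missing IBS-QOL scores, so it is used here only as a scale.

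**Rule set against schedule.**
- Week 4 missing: the last scheduled score is week 0.
- Week 6 missing, week 4 present: the last score is week 4, on treatment.
- Both missing: week 0 fills both.

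**Equal loss.** Let a fraction d in each arm miss week 4, unrelated to outcome, with change set to 0. The expected mean change in an arm is (1 − d)μ, so the difference is multiplied by 1 − d. With d = 0.173 the factor is 0.827, and a true difference of 5 points becomes 5 × 0.827 = 4.1. At 10% missing the factor is 0.90 and at 5% it is 0.95. No SD is needed for this step.

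**Power at equal loss.** Assumed: SD of change 15, 150 per arm, true difference 5 points. With zeros filled in, the variance in an arm is (1 − d)·15² + d(1 − d)·μ², which depends on how much each arm improves. Observed cases only, 124 per arm: SE = √(2 × 225/124) = 1.905 and power is 75%.

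| Placebo mean improvement | Power with LOCF |
|---|---|
| 0 | 74% |
| 5 | 73% |
| 10 | 70% |
| 15 | 65% |

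The power cost therefore runs from under 1 to about 9 percentage points.

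**Unequal loss, no treatment effect.** Both arms improve by μ. The expected false difference is μ × (placebo loss − active loss), with the variance as above. The splits 25%/9.7% and 20%/14.7% each keep the total near 52, but the splits themselves are assumptions.

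| μ | Loss placebo / active | False difference | False-positive rate |
|---|---|---|---|
| any | equal | 0 | 5% |
| 10 | 20% / 14.7% | 0.5 | about 6% |
| 5 | 25% / 9.7% | 0.8 | about 8% |
| 10 | 25% / 9.7% | 1.5 | about 16% |
| 15 | 25% / 9.7% | 2.3 | about 27% |

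For the fourth row: 10 × (0.25 − 0.097) = 1.53. The variances are 0.75 × 225 + 0.25 × 0.75 × 100 = 187.5 and 0.903 × 225 + 0.097 × 0.903 × 100 = 211.9. SE = √((187.5 + 211.9)/150) = 1.63, the expected z is 0.94, and the rejection rate at ±1.96 is about 16%. Reversing the split reverses the sign.

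**The case against.** **A withdrawal score may exist.** Section {18b} has the latest outcomes recorded at withdrawal. If that includes IBS-QOL, an early leaver's last value is a withdrawal score and not baseline. A reader might infer that everyone missing week 4 is entered with exactly no change; the documents do not support that for every patient, because {18b} leaves the instruments open. An early score carried to week 4 would still come from a different time point. The section on withdrawal at participant request also continues follow-up for patients who stop after symptom relief, so stopping treatment need not mean a missing visit.

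**Zero change may be intended.** Patients who ask to quit are recorded as treatment failures, and a no-benefit value fits that spirit. Whether this counts as bias depends on the effect being estimated. But the label assigns no IBS-QOL score, and it does not cover scores missing for other reasons.

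**A per-protocol analysis is planned.** It rests largely on observed week-4 data and could show how much depends on LOCF. It selects compliant completers and does not repair the FAS analysis.

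**Stool data.** A reader might infer that microbiota and metabolite profiles will also be filled from baseline, since "Stool samples of subjects will be collected at baseline (week 0) and the end of treatment period (week 4") and the rule is unrestricted. No section says that these data are imputed, and their handling may well be left to the statistical plan. That reading is not part of the error.

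**Size.** The larger false-positive rates need a marked imbalance in loss and a sizeable improvement in both arms. Milder settings stay close to 5%.

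**Conclusion.** The point holds for IBS-QOL. The protocol commits to a single unrestricted rule that does not suit the three scheduled assessments: a missing week-4 score normally becomes the pre-treatment score (or possibly an early withdrawal score), and a missing week-6 score becomes the on-treatment one.

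The shrinkage to about 83% assumes that the whole 17.3% allowance is missing at week 4, equally in both arms and unrelated to outcome, with baseline carried forward for all of them. The range of false positives from 5% to about 16% also assumes an SD of 15, a 10-point improvement in both arms and the loss splits shown; none of these is in the documents. LOCF cannot be defended here as always conservative, because the direction of bias follows whichever arm loses more patients.

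Only a secondary outcome is touched. The primary responder endpoint, built from the daily diary, lies outside this point, and no sample-size figure changes.

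**What to change.** In sections {20b} and {20c}, remove IBS-QOL from LOCF. Analyse weeks 4 and 6 together in a mixed model for repeated measures on observed data, with treatment by visit and the baseline score, or use multiple imputation. Keep the carried-forward analysis as a sensitivity analysis. State in {18b} whether IBS-QOL is among the outcomes recorded at withdrawal.

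As a clarification only, add that LOCF does not apply to stool microbiota and metabolites, and that patients with observed week-0 and week-4 samples are analysed.

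The cost is wording and standard SAS code, with no change to sample size or visit schedule. The downside is that the main IBS-QOL analysis then assumes data missing at random, which the sensitivity analysis helps to probe. Section {27} has the statistical plan finished before database lock, so the change can be made there before the data are final.
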